#### Aim 1 Recruitment

Participants are recruited via RDS, given demonstrated benefits to (1) potentially recruit a more representative sample and (2) reach deep into social networks to recruit participants who are often not reached through outreach, venue-based, or snowball sampling methods for engagement in HIV testing [6,7,9]. In this method, 8 to 10 MSM and TW seeds will be recruited by study investigators. Seeds, who begin recruitment, are individuals who represent a range of characteristics and are well-networked within the MSM and TW population. The study team works with local CBO partners in Yangon to identify MSM and TW seeds. Seeds complete the first visit study activities and are then given a maximum of 3 coupons with which to recruit their peers from within their social or sexual networks. These peers are invited by the seed to present to the study office with their coupon for participation in the study. If eligible and after completing baseline study activities, the recruited participant may, in turn, become a recruiter. Participants who agree to become a recruiter undergo recruitment training and receive a maximum of 3 coupons for distribution. This process continues until the sample size has been reached. This sampling method has been successfully used by the research team for several research studies of HIV among MSM, including in Malawi and Russia [7,39,40]. RDS has also been used by other investigators to research HIV among people who inject drugs, MSM, and TW in Myanmar [41,42].

Recruitment coupons are prenumbered with a unique coupon number prior to distribution (Figure 3). Coupons contain other information including the study telephone number, site operating hours, and coupon expiration date. There is no information on the coupon that could be used to identify the holder as MSM or TW and no personal information is recorded on the coupon. Coupons are collected from recruited candidate participants at the study site at the time of eligibility screening and the returned coupon number is recorded. Coupons allow for the research team to trace the recruitment process and create analytical weights for the sampling process.

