Study staff keep confidential phone numbers and first names of potential participants for scheduling purposes only. One hard copy of the contact list is stored in a locked cabinet and an electronic version is saved in the electronic tracking system, separate from study data. Only staff members tasked with scheduling participants have access to the electronic list, by permission of the in-country principal investigator. The staff are instructed not to leave any voice or text messages with participants, to verify the identity of the individual, and to not mention any potentially stigmatizing behavior or HIV status during the phone conversations. When the study is mentioned over the phone or while reminding participants of an appointment, it is referred to as a health and wellness project.

Unique identifiers will be used to link study data and are constructed for all participants using information known only to the participant; these will be created to link all surveys, specimens, and laboratory results. The code is formulated from questions that are easily answered, reproducible, culturally appropriate, individually unique, and that MSM and TW will be comfortable answering. The unique identifier is an 8-digit reproducible alphanumerical code developed using the using the first 2 letters of the participant’s last name, the first 2 letters of the participant’s first name, the first 2 letters of the participant’s father’s first name, and last 2 digits of the participant’s birth year. Burmese names are Romanized to English letters based on a transliterated chart of the Myanmar alphabet for purposes of creating a unique ID. During the process of creating the unique ID code with the participant, the study team member indicates that the participant only needs to respond with the appropriate numbers or letters to the question and do not need to give the full response (eg, participant only needs to provide the first letter of the city where he or she currently lives rather than state the full name of the city). Doing so provides an additional layer of privacy for the participants. This unique identifier can be recreated throughout the study and will facilitate linking study participants with biological results while maintaining anonymity. This process has been successfully used in past research studies conducted by this study team [39,50].

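### The code that links specimens and HIV results is described as unique and known only to the participant, but six name letters and two birth-year digits guarantee neither

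*Protocol article*

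**What the plan says.** All of this stands in the protocol article, mainly under Human Subjects Considerations.

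- Purpose and basis: identifiers are "constructed for all participants using information known only to the participant; these will be created to link all surveys, specimens, and laboratory results".
- Claimed property: "The code is formulated from questions that are easily answered, reproducible, culturally appropriate, individually unique".
- Definition: "The unique identifier is an 8-digit reproducible alphanumerical code developed using the using the first 2 letters of the participant’s last name", followed by two letters of the first name, and then "the first 2 letters of the participant’s father’s first name, and last 2 digits of the participant’s birth year".
- Preparation of the letters: "Burmese names are Romanized to English letters based on a transliterated chart of the Myanmar alphabet".
- Use over time: "This unique identifier can be recreated throughout the study and will facilitate linking study participants with biological results while maintaining anonymity".
- Worked example of a partial answer: the "participant only needs to provide the first letter of the city where he or she currently lives".

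One other number is described, under Aim 1 Recruitment: "Recruitment coupons are prenumbered with a unique coupon number prior to distribution". The number is recorded when the coupon is returned. Its stated use is to trace recruitment and build the sampling weights, not to link specimens. Seeds are exempt from needing a coupon (Aim 1 Study Sample).

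**The concern.** The two claimed properties do not follow from the definition. Names and birth years are shared attributes, and the article states no duplicate check, serial number or second linking key. The information is not exclusive to the participant either: the same section has staff holding first names for scheduling, and Aim 1 Recruitment has participants recruited by peers from their own social or sexual networks.

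Two different errors are possible:

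- **Merge.** Two participants share a code, and a result is attached to the wrong one.
- **Split.** One participant's name is Romanized differently at a later visit, and a result fails to link.

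The link carries weight. According to Aim 1 Data Collection and Aim 1 Follow-Up, the dried blood spot (DBS) result confirms the self-reported result and gives the team a result for people who do not return. It also prompts recontact of infected non-returners, sends discordant results to Western blot, and supports entry to Aim 2. CD4 and viral load results in Aims 2 and 3 rely on the same code.

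**Working it through.** **1. The plan's own figure.** The article gives no figure for uniqueness of the code. The only plan figure that enters is the Aim 1 sample size. With 60% against 75%, two-sided alpha 0.05 (two-sided is assumed), 80% power and a continuity correction, the calculation gives 165 per arm, or 330 in total, as stated. Allowing for 10% non-response, 330 / 0.90 = 366.7, against 366 stated. The sample size is not in dispute.

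**2. Claims against components.** The components are last name (2 letters), first name (2), father's first name (2) and birth year (2 digits), which makes 8 characters. City of residence is not among them, so the example contradicts the definition. This needs no assumption.

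**3. Chance of a shared code.** The number of pairs among n = 366 is n(n − 1)/2 = 366 × 365 / 2 = 66,795. With K equally likely codes, the expected number of pairs sharing a code is E = 66,795 / K, and the chance of at least one is P = 1 − exp(−E). Take K = k³ × y, where k is the effective number of two-letter values per name part and y the effective number of birth years. The documents give neither k nor y. Every row except the first, which is the uniform reference, is an assumption.

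| k | y | K | E | P |
|---|---|---|---|---|
| 26² = 676 (uniform) | 100 | 30,891,577,600 | 0.0000022 | about 2 in a million |
| 50 | 20 | 2,500,000 | 0.027 | 2.6% |
| 30 | 20 | 540,000 | 0.124 | 12% |
| 20 | 15 | 120,000 | 0.557 | 43% |
| 15 | 15 | 50,625 | 1.32 | 73% |
| 10 | 15 | 15,000 | 4.45 | 99% |

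The uniform row is a floor, because name initials and adult birth years are not uniform. Which lower row applies cannot be told from the documents.

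**4. Number of people in the code space.** Aims 2 and 3 may also take people from outside Aim 1 (Aims 2 and 3 Study Sample). In the extreme case that all 54 Aim 2 places were filled that way, n = 366 + 54 = 420, there are 420 × 419 / 2 = 87,990 pairs, and the 43% row becomes 52%. The choice of k and y matters far more than this.

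**5. Split codes.** No rate can be computed. The article gives no figure for how consistently the code is reproduced.

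**6. What the built-in check catches.** A participant whose DBS and self-reported results disagree is asked for a further blood sample for Western blot (Aim 1 Follow-Up). That can expose a swapped result in someone who returns and reports. It does not reach a wrong result that happens to agree with the self-report, a non-returner who has reported nothing, or a CD4 or viral load result.

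**The case against.** The strongest reply is that this is a journal article. Duplicate rejection, specimen labelling and the layout of the tracking system normally sit in the full protocol or the data-management procedures. The system described under Aims 2 and 3 Data Collection already handles registration and laboratory results and may hold a record number. The article also reports safeguards: a transliteration chart meant to make the code reproducible, a recorded coupon number, Western blot on discordant results, and successful use of the process in earlier studies by the same team. All of this stands as a limit on size. It does not rescue the two stated properties or the example, which are wrong as written whatever the full protocol holds.

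The magnitude is also fairly challenged. The assumed rows run from 2.6% to 99%, and a shared code is not the same as a wrong HIV result. At the plan's 15% prevalence, and if status is independent of code, 2 × 0.15 × 0.85 = 25.5% of sharing pairs would differ in HIV status. In the 43% row that is 0.557 × 0.255 = 0.14 pairs, or a 13% chance of any such pair, before asking whether staff would notice. That discount applies to HIV results only; CD4 and viral load values can differ between two people of the same status.

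Two stronger readings are tempting. A reader might infer that the code authenticates a person asking for a result, so that a recruiter who knows the items could obtain it. No section gives the code that role, and staff are separately told to verify identity on calls. A reader might also infer that the primary Aim 1 comparison is compromised. Completion of testing is defined by receipt of results from the assigned method and reported awareness of status (Aim 1 Data Collection), not by DBS, and no effect on that comparison has been shown.

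**Conclusion.** The point holds as a defect in a stated linking rule. The code is neither guaranteed unique nor exclusive to the participant, the city example does not belong to it, and it is the only link the article states for surveys, specimens and laboratory results. Mislinkage and failed linkage are possible, and the Western blot step covers only part of that.

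The size is uncertain and rests wholly on assumed name and birth-year concentration: about 2 in a million under uniform codes, about 3% to 43% under moderate concentration, and higher if names are very concentrated. No expected number of mislinked results can be claimed. What makes the change worthwhile is the consequence of a single error (an HIV result attached to the wrong person, or an infected non-returner not traced) set against a very small cost.

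**What to change.** 1. Have the existing tracking system assign a sequential study number at registration. Use it together with the self-generated code as the linking key and on specimen labels.
2. Flag duplicate codes at registration. Enrolment was under way when the article was written, so also check the records already held for duplicates.
3. Keep the recorded coupon number as a cross-check. It cannot be the key itself, because seeds have none.
4. Delete the claim that the information is exclusive to the participant, describe the code as reproducible rather than unique, and reconcile the city example with the listed components.
5. If the full protocol already provides a record number or duplicate check, say so in the text; item 4 is still needed.

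The number serves the records. Participants should not have to present it before a result is released, since that could delay results. The cost is one extra field, one duplicate check and revised label wording, with staff looking up the number at return visits. Where a code is flagged as shared, the lookup needs the coupon number or the registration record to separate the two people.

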## Results

Formative, qualitative research was completed between June and September 2015. This included 12 MSM and 13 TW in-depth interview participants, as well as 12 MSM and TW participants and 23 service providers and community leaders participating in focus group discussions [36].

Participants provided logistical input, particularly as it related to location of the study office, recommending that the office be in a neighborhood in the center of the city and directly accessible by most bus lines. Participants also provided insights into social considerations for providing HIV testing, prevention, and care for MSM and TW populations in Yangon; opinions, preferences, and concerns about HIVST; and experiences and perceptions of HIV treatment and care. Generally, both MSM and TW described concerns about discrimination and stigmatization of MSM and TW populations within government health systems, often preferring to use nongovernmental community-based services that are an expanding presence in Yangon. Regardless of general perceptions that MSM and TW were at high risk for HIV acquisition and emerging options for HIV testing and care, MSM and TW participants described hesitation about HIV testing that was often related to fear of being seen in a testing facility that would unintentionally disclose one’s HIV status, gender, or sexual identity.

The privacy and convenience offered by HIVST garnered significant interest from a majority of focus group participants, many of whom indicated the appeal of using these kits in the privacy of their own homes. This interest was weighed, however, against concerns that incorrect use could produce an inaccurate result and that lack of pretest counseling could lead to unintended adverse effects such as suicide by someone who receives a positive result. A further concern was that users would not be effectively linked to care following a positive diagnosis. These findings led to concrete protocol changes for the subsequent self-testing intervention. Specifically, in collaboration with OraSure, we developed new Myanmar language instructions for use, included a sticker on all packaging that provided a 24-hour telephone number in the case of questions or concerns, and included provision of pretest counseling for participants that included linkage to services when participants were provided with the self-test at the study office.

MSM and TW qualitative participants also described a variety of challenges in moving through the HIV care continuum. Despite a significant increase in availability of ART in Myanmar in the past 5 years, the majority of participants reported issues with staging, treatment, and care, which can delay treatment initiation and inhibit adherence. Participants expressed frustration with current health system structure; many described having to visit different clinics and hospitals for testing, staging, treatment, and monitoring as well as having repeated confirmatory tests at each provider they visited.

MSM and TW participants expressed a strong preference for treatment and care services that are friendly, discrete, and convenient. Long travel times and cost, limited clinic hours, and unfriendly staff were described as barriers by many participants, especially when they are required to visit different providers for testing, staging, and treatment. In response, the research protocol was adjusted to include night and weekend office hours, the project office was chosen because of its central location and proximity to bus lines, and MSM and TW office staff were hired to create a nonstigmatizing and welcoming environment.

Qualitative participants also voiced concerns that home visits by peer navigators could expose their HIV status to their family or the community. To protect the privacy of the participants who enroll in peer navigation, we adapted the protocol to allow peer navigators to visit participants in any mutually agreeable location. This flexibility allows the participant to determine if, how, and when they would like to disclose their status to family and friends and minimizes the chance of unintentional disclosure.

Following the qualitative research, Aim 1 recruitment began in November 2015 with subsequent enrollment into Aims 2 and 3, and study activities for the 3 aims are currently ongoing. Broader social changes have since led to further modification of the above protocol. First, during the development of the intervention protocol the government of Myanmar adjusted the ART guidelines to reflect the importance of early detection and treatment in key populations at risk of HIV infection [52]. Recent updates to the WHO guidelines have since prompted the government to change this strategy and promote immediate ART initiation for all key populations, including MSM and TGW, regardless of CD4 count [28,53]. Our protocol had initially focused on the inclusion of ART-eligible MSM and TW in Aims 2 and 3; however, these policy changes made all newly diagnosed participants eligible for ART. Thus, the research plan was adjusted to incorporate this change, and all participants found to be living with HIV are referred to treatment and care programs and offered peer navigation assistance.

Throughout the implementation of this study, many nongovernmental organizations in Yangon have begun to offer home visits and peer support programs for clients who are on ART. Given the recent popularity of such programs and potential competition between this study and ongoing programs, we further altered the procedures in Aim 3, allowing participants to use our peer navigation services or, alternatively, use external peer navigation services from organizations providing the participant’s ART. Additional survey items were subsequently developed to capture data about types and frequency of services participants receive from these organizations to use in the comparison of peer navigation versus declined navigation.

## Discussion

This study seeks to identify successful and acceptable methods to address losses in the HIV care continuum among MSM and TW in Myanmar. Formative, qualitative research has been completed and was used to further refine the study protocol and interventions. Qualitative research identified several perceived benefits and concerns related to HIVST, which allowed us to ensure instructions of HIVST were understandable to participants and that participants had appropriate pretest counseling prior to HIVST and were linked to counseling and services following testing. Additional identification of barriers and facilitators to HIV care, ART initiation, and adherence during qualitative research allowed for further refinement of the intervention and study procedures. Following the completion of the formative research, enrollment into Aim 1 began in November 2015 with subsequent enrollment into Aims 2 and 3 with prospective follow-up for participants with biologically confirmed prevalent or incident HIV infection and who had not previously been engaged in care. These participants are being followed to determine the impact of CD4 POC and peer navigation on ART initiation and virologic suppression.

Early identification of HIV infection, engagement in care, and ART adherence are critical components to provide both therapeutic benefits for people living with HIV and to reduce onward transmission of HIV among at-risk populations [54]. The National AIDS Program in Myanmar has recognized the urgent need to respond to the HIV epidemic that is concentrated among MSM, TW, and other key populations; however, innovative methods to overcome stigma and provide access to HIV testing and care services are needed. The growth of the nongovernmental organization community in Myanmar, coupled with the increasing implementation of and capacity for innovative methods, can very well support these national efforts and may have aggregate effects against the HIV epidemic among MSM and TW.

## Appendix

Multimedia Appendix 1 Reviewers' comments.

## Abbreviations

3 MDG: Three Millennium Development Goals Fund
amFAR: Foundation for AIDS Research
ART: antiretroviral therapy
CBO: community-based organization
DBS: dried capillary blood spot collection
FDA: Food and Drug Administration
HIVST: HIV self-test
HPTN: HIV Prevention Trials Network
JHU: Johns Hopkins University
LGBT: lesbian, gay, bisexual, and transgender
MSM: men who have sex with men
PEPFAR: United States President's Emergency Plan for AIDS Relief
POC: point-of-care
RDS: respondent-driven sampling
TW: transgender women
VCT: voluntary counseling and testing
WHO: World Health Organization
